## Abstract

**Background:**

It is generally recognized that existential concerns must be addressed to promote the dignity of patients with advanced cancer. A number of interventions have been developed in this regard, such as dignity therapy and other life review interventions (LRI). However, so far, none have focused on a positive approach or evaluated its effects on dignity and personal growth. This study aims to explore the feasibility of Revie ⊕, a life review intervention comprising a positive, patient-centered approach, and to determine potential changes of patients’ sense of dignity, posttraumatic growth, and satisfaction with life.

**Methods:**

A mixed method study will be performed, which includes specialized nurses and 40 patients with advanced cancer in an ambulatory and in-patient setting of a Swiss university hospital. Quantitative methods involve a single group, pre- and post-intervention, and outcome measurements include the Patient Dignity Inventory, the Posttraumatic Growth Inventory, and the Satisfaction with Life Scale. Feasibility data relating to process, resource, and scientific elements of the trial will also be collected. A semi-directed interview will be used to collect qualitative data about the process and the participants’ experiences of the intervention. In this way, enhanced quantitative-qualitative evidence can be drawn from outcome measures as well as individual, contextualized personal views, to help inform researchers about the plausibility of this complex intervention before testing its effectiveness in a subsequent full trial.

**Discussion:**

Patient dignity is a goal of quality end-of-life care. To our knowledge, this is the first trial to evaluate the role of a life review intervention that is focused on personal growth and on changes relating to the experience of having cancer.

This study will evaluate the feasibility of a novel intervention, Revie ⊕, which we hope will contribute to promote the dignity, personal growth, and overall life satisfaction of patients with advanced cancer.

**Trial registration:**

ISRCTN, ISRCTN12497093

**Electronic supplementary material:**

The online version of this article (doi:10.1186/s40814-016-0101-z) contains supplementary material, which is available to authorized users.

## Background

Approximately 37,000 new cases of cancer occur annually in Switzerland. Despite advancements in medical technology, cancer remains the second leading cause of mortality (about 16,000 individuals per year) in Switzerland [1]. Patients with advanced cancer often experience significant levels of existential distress [2, 3]. According to Kissane [4], existential distress represents a person’s distress when facing his/her own mortality, which brings out feelings of helplessness, lack of sense, discouragement, or remorse. Existential suffering is one of the most exhausting conditions at the end of life [5]. There is a paucity of interventions focusing on relieving spiritual or existential concerns [2]. However, it is recommended to consider the patients’ and families’ values and beliefs; to help patients and families in sharing their emotions and time; and to support patients and families in carrying out realistic projects [6, 7]. Interventions that relieve existential distress support patients’ dying with dignity [8, 9]. In end-of-life care, dying with dignity constitutes an important aim, but this concept has multiple meanings. According to Guo and Jacelon [10], dying with dignity includes a dying process with minimal symptom distress, being human and being self, achieving existential and spiritual goals, and maintaining meaningful relationships with significant relatives*.*

Dignity at the end of life is a major concern of health professionals in care of people with advanced cancer [11]. Nurses are most in contact with patients facing life-threatening disease and they play a specific role in providing quality of life, supporting health and well-being [12, 13].

Despite continued developments and improvements in palliative care in Switzerland, nursing interventions promoting patient dignity are still insufficiently available in routine clinical practice. To date, little empirical research has focused on interventions to address existential distress [2]. One way of addressing these needs and enhancing dignity during the end of life is a therapeutic life review intervention (LRI) [14]. This set of interventions consists of evoking memories, personal life events, and accomplishments. It is a structured process of reinterpreting life existence [15].

LRIs in palliative situations have been shown to have positive effects on quality of life [16, 17], spiritual well-being [18], depression [19, 20], and death-related anxiety [21]. The main perceptions of patients are reconsideration and acceptance of the uniqueness of their lives, finding meaning, defining future projects, reconciliation with their past experiences [22], and the satisfaction of leaving a personal legacy [23]. Change also occurs within the family in terms of perception, satisfaction [23–25], communication, and cohesion [26, 27].

Despite cancer being widely seen as an adverse event, some cancer patients report having experienced a degree of personal growth that caused them to change their values and relationships in positive ways. Tedeschi and Calhoun [28, 29] defined this phenomenon as posttraumatic growth (PTG). It refers to the positive psychological change experienced as a result of struggles with highly challenging life circumstances. In the context of experiencing advanced cancer, PTG is documented. Changes can occur through the intensification of human relationships, a better outlook on life [30], greater religious satisfaction, increased compassion, and concern for others [31]. The main positive outcomes of PTG are decreased psychological distress [32] and depression [33, 34], as well as enhanced levels of general [31, 35] and spiritual well-being [33].

While some LRIs have already been shown to have a benefit at an existential level among individuals with advanced cancer, none, to our knowledge, are relying on an approach centered on personal development, although it has been shown that PTG can have a positive influence on the well-being of patients with advanced cancer [8]. Moreover, this type of intervention has not yet been tested in the context of specific conditions and circumstances that may be encountered in Switzerland.

In our current research, we propose to develop a specific LRI to promote existential needs in advanced cancer patients. We used the MRC framework for the development of complex interventions [36] with the aim to build on the World Health Organization’s (WHO) recommendations for palliative care that emphasize the importance of spiritual well-being. The intervention is called Revie ⊕. It focuses on personal resources as well as changes in relationships and values since the time of diagnosis. The intervention is patient-centered and consistent with the patient’s needs, values, and preferences. Orienting the intervention to include a positive approach, namely to expand on the positive changes brought on by the cancer experience, could contribute to promote dignity, personal development, and a higher degree of overall life satisfaction.

The purpose of the present study is to assess the feasibility of the Revie ⊕ intervention and to evaluate potential changes in dignity, posttraumatic growth, and satisfaction of life for patients with advanced cancer in order to obtain data for a future effectiveness trial.

## Methods/design

### Aim/objectives

The overall aim of this study is to evaluate the feasibility of Revie ⊕, a new LRI intervention aimed at patients with advanced cancer within the ambulatory and in-patient setting of a university hospital in the French-speaking part of Switzerland, and to evaluate potential changes in dignity, posttraumatic growth, and satisfaction with life.

Our primary objectives relate to the assessment of the feasibility of the proposed recruitment strategies and outcome assessment protocols:Determine recruitment and retention rates and identify best strategies for recruitment and retention in this patient population (if 40 participants are recruited over 12 months and with 80 % having completed follow-up, the intervention is considered feasible).Determine the acceptability of the intervention for the patients, in terms of:Engagement and compliance with the protocolPerceptions of barriers and facilitators considering the sensitive and intimate topic and the particular vulnerability of the population with life-threatening diseaseThe degree of satisfactionThe perceived relevance of the intervention
Explore the acceptability for nurses delivering the intervention in terms of fidelity (adherence structured content), resources mobilized, perception of barriers, and facilitators, considering the sensitive and intimate discussion and practice change.Estimate required sample size for a future larger effectiveness trial.

The secondary objectives will be to assess the impact of Revie ⊕ on the sense of dignity, posttraumatic growth, and satisfaction with life for patients with advanced cancer and to determine the most appropriate outcome for a future larger trial.

### Study design

We propose a pilot pre-post feasibility study using a mixed method approach, i.e., an embedded concurrent design with both quantitative and qualitative parts [37].

The quantitative part of the study consists of a single pre-post-intervention group. The qualitative method is nested within the predominant quantitative part and includes semi-directed interviews with the patients to obtain data on the intervention process and participants’ experiences and views.

Questionnaires and a focus group interview are used to explore the health professionals’ acceptability.

An embedded concurrent design has been chosen because the combination of quantitative and qualitative methods will provide more information about the barriers for participation, and an estimated response rate. This study will also help us to better understand the impact of the intervention on the participants (willingness, unanticipated experiences during the trial, resources that can facilitate to conduct the intervention, the feedback of the patients and nurses about the intervention delivery). The use of a mixed method is recommended to improve interpretation of the results in palliative care research [38, 39]. RCT may not be the most appropriate design because of practical and ethical obstacles. At this stage, we did not opt for a control group as we did not intend to measure effectiveness in the first place. Our main purpose was to develop a theory-based intervention, determine the patients’ perception and satisfaction with the intervention, explore the patients’ adhesion to the intervention, determine the appropriateness of the outcome measures, and identify the adequacy of time, location, and process. In addition, it was important to explore the emotions associated with this intervention through the discussion of this intimate and sensitive topic.

### Study setting

A purposive sample of 40 patients with advanced cancer will be recruited within the ambulatory and in-patient setting of a university hospital in the French-speaking part of Switzerland. As it is a pilot study, and the intervention has not been tested previously, no formal sample size calculation was conducted [40]. The sample size was based on the recommendations by Hertzog [41]: a sample of 20–40 persons is adequate for a pilot study employing a single group to ultimately estimate the sample size for a future trial.

This preliminary study reviews the recruitment; checks the feasibility and the appropriateness of the instruments used and the sample size required for a subsequent larger study; and examines how the process (timing, duration, etc.) could eventually be consolidated [36, 42]. Difficulties of recruitment and retention are reported by similar studies, particularly concerning advanced cancer patients and studies over 12 months. However, considering that approximately 800 persons consult annually in the two participating settings and that 40 % of these persons are potentially eligible for the study and estimating an 80 % refusal, it seems feasible to recruit a total of 40 participants.
*Inclusion criteria*: adults (aged 18 years or older) with advanced cancer (T3 or T4, or the presence of metastases), with an adequate health status to participate in the study, as determined by clinical consensus between nurses and physicians, and who are able to cognitively understand and consent to inclusion in the study
*Exclusion criteria*: patients diagnosed with cognitive disorders related to memory loss or disturbances of speech that would not allow for a constructive exchange, and people with insufficient command of the French language to complete the study questionnaires

### Recruitment

Recruitment began in April 2015 and will take place over a 12-month period. Information was given prior to the commencement of the study to all the nurses, head nurses, and oncologists of the services. A factsheet was also made available to them. They all have a role to play in informing patients about the study. Eligible patients are invited by the nursing staff to participate in the study. They are subsequently contacted by the researcher(s), who provides an overview of the study and presents the information letter and consent form to the potential participant. A minimum of 24 h is given to the participant to sign the consent form.

Regular meetings are planned between the research team and the staff to identify and overcome any difficulties encountered during this phase to enhance recruitment. To date, 30 participants have been recruited.

### Study overview

The study consists of three stages (Table 1): the pre-intervention phase (T0), followed by the intervention (T1), and, after its completion, the post-intervention phase (T2). In light of recommendations by other investigators who have implemented a similar intervention focused on life review [16, 17], the time between T0 and T2 will be limited to a maximum of 1 month. This timeframe takes into account the rate of potential loss of participants due to their lower general health status or as a result of patient death, and the fact that the effects on the sense of dignity, life satisfaction, and posttraumatic growth appear to occur fairly soon after the intervention.

**Table 1 Tab1:** Study procedure

T0: pre-test	T1: intervention		T2: post-test	
Quantitative	Session 1	Session 2	Quantitative	Qualitative
Sociodemographic + health data PDI^a^, SWLS^b^, PTGI^c^	Encounter with trained nurse to share life history + positive approach	Presenting and finalizing the booklet	Acceptability questionnaire PDP, SWLS, PTGI	Semi-structured interview about the process

*PDI* Personal Dignity Inventory, *SWLS* Satisfaction with Life Scale, *PTGI* Posttraumatic Growth Inventory

^a^Chochinov et al. [43]

^b^Diener et al. [50]

^c^Tedeschi and Calhoun [46]

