### Description of the intervention

A brief life review intervention (Revie ⊕) was developed based on a literature review and a theoretical model focusing on a positive patient-centered approach. Revie ⊕ allows specialist nurses to talk about life events with cancer patients, explore how the diagnosis has changed their values and preferences, and discuss ultimate life goals or projects. As an outcome of this LRI, a booklet will be created by integrating the patient’s significant elements evoked during the intervention. The intervention is delivered by eight nurses, all of whom are certified in oncology care, have received specific theoretical and evidence-based knowledge, and have the specific skills needed to deliver a life review intervention. These nurses are part of the staff. However, these nurses have time to deliver the intervention. The intervention consists of two sessions scheduled in mutual agreement between nurse and patient, but above all favoring an appropriate time for the patient. The face-to-face interview constitutes a moment completely centered on the patient’s experience. This face-to-face interview takes place in a space reserved for this purpose. In order to conduct the interview, the nurses follow a predefined guideline that permits them to be in authentic presence with the participants. The first session (T1) lasts for approximately 60 min and allows participants to share significant events about their life history as well as supports personal development by focusing on positive changes that have occurred since the cancer diagnosis. Five domains are addressed during this session: (1) a reflection of the patient’s life story and specific significant events; (2) a focus on the positive changes that have occurred since the diagnosis; (3) an expression of the patient’s values and vision of life (accentuating the strengths and resources) and the patient’s relationship with others; (4) a discussion of significant issues (i.e., what patients want to communicate with their relatives, or determining the project, which is most important to carry out); and (5) a discussion of the patient’s deepest concerns and his/her thoughts about death and dying. Throughout the intervention, nurses value patients’ coping strategies, strengths, and resources. The changes brought about by the patients’ experience of cancer on themselves and their life vision and values as well as their relationship with others are at the center of the intervention.

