At the end of the interview, the participant is asked to send pictures, poems, or drawings that he considers important to the researcher. The tape recordings of the session are transcribed by the research team. Thus, a detailed account of the patients’ life events and experiences are obtained. Based on these transcripts, a booklet is created by the research team. The booklet consists of about 12 pages in A5 format and covers four sections: (1) my significant life events and the significant persons in my life; (2) my experience of cancer; (3) my values/life vision/changes; and (4) my project(s). Each booklet is personalized by highlighting its unique style with chosen words (we strive to be as close as possible to patients’ words and expressions). According to the patients’ wishes, texts, poems, pictures, or citations are integrated into the booklet.

The second meeting (15–30 min duration) is arranged to present, complete, if necessary change, and finalize the booklet. Patients who did not send photos, poems, or any other text before can include these at this moment. Patients are fully integrated as main actors of this process. If needed, another meeting is scheduled to revise the booklet. The final version of the booklet is validated by the patient before printing and delivering.

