### Qualitative part

At the end of the intervention and after completing the post-test questionnaires (T2), a semi-structured interview will be conducted by the researcher, which lasts for about 30 min. This interview focuses on the experience of the intervention and the process.

The following questions are addressed: “You shared your life perspectives and finalized a booklet. What do you think and feel about the whole experience and the process? What feelings did you experience most intensely during the process?”

The nurses are also invited to keep a notebook in which they can note their difficulties and their emotions. These writings will be transcribed and a thematic analysis will be performed. To gather more detail about their intervention experience, a focus group will be led by two facilitators who are external to the research.

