#### Quantitative part

Data analysis will be performed using Stata Software Stata©. Descriptive statistics (mean, median, standard deviation) will be calculated for sociodemographic data. Analyses will be carried out on all available patient data with data at baseline and at the end of the study intervention. We will report descriptive findings concerning recruitment numbers, completions, drop-out rates, and missing data. Quantitative data will be cleaned, i.e., checked for out of range values and missing values. For >10 % of missing values, the subject will not be considered. Distribution of variables will be checked for normality using box plot, skewness and kurtosis, and test of normality. The data will be summarized with standard descriptive measurements. Continuous variables will be summarized by their mean and standard deviation, categorical variables as numbers and percentages, and presented with 95 % confidence intervals.

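### T2 is planned only after the intervention is completed, so patients who stop early have no planned outcome assessment and the pre-post results describe completers only

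*Protocol article*

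**What the plan says.** All references are to the protocol article.

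- **Schedule.** Study overview sets out a pre-test (T0), "followed by the intervention (T1), and, after its completion, the post-intervention phase (T2"). Table 1 puts T2 after Session 2. The same section adds that "the time between T0 and T2 will be limited to a maximum of 1 month".
- **What completion means.** Under Description of the intervention, "The intervention consists of two sessions scheduled in mutual agreement between nurse and patient", and "The second meeting (15–30 min duration) is arranged to present, complete, if necessary change, and finalize the booklet". A further meeting is possible, and the patient validates the final booklet.
- **Timing of the post-test.** Qualitative part: "At the end of the intervention and after completing the post-test questionnaires (T2), a semi-structured interview will be conducted".
- **Analysis set.** Under Data analysis, Quantitative part, analyses use "all available patient data with data at baseline and at the end of the study intervention". The next sentence promises descriptive reporting of recruitment, of how many complete or drop out, and of missing values.
- **Decision rule.** Aim/objectives: "if 40 participants are recruited over 12 months and with 80 % having completed follow-up, the intervention is considered feasible". Patients' engagement and compliance are listed as a separate aspect of acceptability, with no threshold. Estimating the sample size of a later trial is also a primary objective.

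**The concern.** The schedule, the interview timing and the analysis set all tie the post-test to the end of the intervention. None of them plans a T2 for a patient who has session 1 but does not reach a finalized booklet, even if that patient could and would fill in the PDI, SWLS and PTGI.

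Two things follow. First, the estimated changes and their standard deviations describe patients who finished the intervention. If the later trial analyses everyone enrolled, which the article does not state, those inputs come from a selected group. Second, one of the stated purposes is to judge the feasibility of outcome assessment. For patients who stop early, that question goes unanswered, and the 80 % figure counts them together with patients who finished the booklet but gave no T2 data.

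**Working it through.** **The plan's own figures.** Study setting gives 800 patients a year, 40 % eligible and 80 % refusing: 800 × 0.40 × (1 − 0.80) = 64, which covers the 40 needed. Taking the 40 enrolled as the denominator, the retention threshold is 0.80 × 40 = 32. No power calculation was made, so there is none to reproduce.

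**What the schedule implies.** Let c be the proportion completing the intervention, q the T2 return among completers, and r the T2 return among non-completers if they were asked.

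- As scheduled: proportion completing follow-up = c × q. It can never exceed c.
- With T2 offered to all: T2 return = c × q + (1 − c) × r.

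The article gives none of c, q or r, so the values below are assumptions. Probabilities are P(X ≥ 32) for X ~ Binomial(40, p).

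| c | q | as scheduled, p = cq | P(≥ 32) | T2 return if r = 0.50 | P(≥ 32) |
|---|---|---|---|---|---|
| 0.95 | 0.85 | 0.8075 | 0.640 | 0.8325 | 0.783 |
| 0.90 | 0.90 | 0.8100 | 0.655 | 0.8600 | 0.902 |
| 0.85 | 0.95 | 0.8075 | 0.640 | 0.8825 | 0.961 |
| 0.80 | 1.00 | 0.8000 | 0.593 | 0.9000 | 0.985 |
| 0.80 | 0.95 | 0.7600 | 0.352 | 0.8600 | 0.902 |

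For c = 0.85 and q = 0.95, other values of r give:

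- r = 0.30: 0.8075 + 0.15 × 0.30 = 0.8525, P = 0.875
- r = 0.70: 0.8075 + 0.15 × 0.70 = 0.9125, P = 0.993

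The first and third rows show the merging: opposite mixes of completion and return give the same 0.8075. The right-hand columns show T2 return alone. They are not the chance of passing a criterion that still requires both.

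**Attrition.** Over all enrolled patients, inflation for loss is 1/p. For c = 0.85 and q = 0.95 this is 1/0.8075 = 1.24. With T2 offered to all and r = 0.50 it is 1/0.8825 = 1.13. The first figure already counts early stoppers as losses.

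**Why the threshold should not move to T2 return alone.** Take c = 0.50, q = 0.95 and r = 0.70 (assumed): 0.475 + 0.350 = 0.825, or 33 of 40. The intervention would pass as feasible although half the patients never finished it.

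**Evidence on frequency.** Study status reports 30 recruited, 27 interventions performed and three still to be delivered. It mentions no early stop and does not report T2 returns.

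**The case against.** The strongest reply is that the article describes the ordinary sequence and nowhere forbids a T2 for someone who stops. It is a condensed account, and the full protocol may provide for such patients. That limits the point to what is planned here. Still, the schedule, the interview timing and the analysis set all agree, so this is a stated schedule and not mere silence.

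A reader might infer that a result below 80 % could not be traced to the intervention or to outcome collection. The documents do not support that. Compliance is assessed in its own right, completions and drop-outs are to be reported, and the team makes each booklet and so knows who finished. Only the T2 return among early stoppers stays unknown.

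A reader might also infer that the attrition figure applies to completers alone. It does not: taken over all enrolled, it counts stoppers as losses. The selection affects the changes and standard deviations.

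Two further replies stand in part. Post-intervention measurement is normal in a single-group pilot that disclaims testing effectiveness, and requiring both the intervention and T2 is a defensible test when the conclusion is that the intervention is feasible. Both are reasons to keep the 80 % rule as it is. Neither is a reason to leave early stoppers unassessed. Finally, the losses that Study overview anticipates are declining health and death, so many early stoppers might be unable to answer. A 50 % reply is purely illustrative.

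**Conclusion.** The point holds as a modest, low-cost improvement. As written, patients who stop before the booklet is finalized have no planned T2, the pre-post changes and standard deviations come from completers, and the feasibility of collecting outcomes after early stopping cannot be learned. The 80 % figure merges two quantities, although one of them, intervention completion, can be described from other planned reporting.

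The size is unknown and may be small. The probabilities above depend wholly on assumed rates and on 40 enrolled as the denominator. They show how the figure behaves and do not predict this study's result.

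**What to change.** 1. **Study overview:** offer the T2 PDI, SWLS and PTGI to every enrolled patient who is able and willing, within the existing one-month T0–T2 limit, whether or not session 2 and the booklet were completed.
2. **Data analysis, Quantitative part:** include these data in an all-enrolled summary, shown beside the summary for completers.
3. **Reporting:** give intervention completion and T2 return as two proportions of all enrolled patients, with their 2 × 2 cross-table.
4. **Aim/objectives:** keep the 80 % criterion, and state that it means completion of both the intervention and T2. Do not apply it to T2 return alone.

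The cost is a wording change, one extra summary, and a slight questionnaire burden for the few patients who stop early, who may decline. With 30 of 40 recruited at the time of the article, the extra T2 offer could still reach the remaining patients, and the two proportions can be reported for all 40 from existing records.
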